## Abstract

**Aim::**

This paper describes the study protocol, which aims to evaluate the effectiveness of a multifaceted intervention package called ‘Enhanced Primary Healthcare’ (EnPHC) on the process of care and intermediate clinical outcomes among patients with Type 2 diabetes mellitus (T2DM) and hypertension. Other outcome measures include patients’ experience and healthcare providers’ job satisfaction.

**Background::**

In 2014, almost two-thirds of Malaysia’s adult population aged 18 years or older had T2DM, hypertension or hypercholesterolaemia. An analysis of health system performance from 2016 to 2018 revealed that the control and management of diabetes and hypertension in Malaysia was suboptimal with almost half of the patients not diagnosed and just one-quarter of patients with diabetes appropriately treated. EnPHC framework aims to improve diagnosis and effective management of T2DM, hypertension or hypercholesterolaemia and their risk factors by increasing prevention, optimising management and improving surveillance of diagnosed patients.

**Methods::**

This is a quasi-experimental controlled study which involves 20 intervention and 20 control clinics in two different states in Malaysia, namely Johor and Selangor. The clinics in the two states were matched and randomly allocated to ‘intervention’ and ‘control’ arms. The EnPHC framework targets different levels from community to primary healthcare clinics and integrated referral networks.

Data are collected via a retrospective chart review (RCR), patient exit survey, healthcare provider survey and an intervention checklist. The data collected are entered into tablet computers which have installed in them an offline survey application. Interrupted time series and difference-in-differences (DiD) analyses will be conducted to report outcomes.

## Introduction

The burden of non-communicable diseases (NCDs) such as cardiovascular diseases (CVDs), chronic obstructive lung diseases, cancer and diabetes affects health and the socio-economic development of countries (Mendis, 2014; Bommer *et al*., 2018; Niessen *et al*., 2018). High systolic blood pressure, fasting plasma glucose and body mass index are the leading risk factors of disability-adjusted life years globally (GBD 2017 Risk Factor Collaborators, 2018). These metabolic risk factors are known to increase CVD which is the main contributor to NCD-related premature death (World Health Organization, 2018). However, the causes of CVDs are largely amenable to change through behavioural modification and risk factors prevention.

A comprehensive situational analysis of the Malaysian health system undertaken in 2016–2018 revealed that the NCD burden is very high and is rapidly increasing with almost two-thirds of Malaysian adult population having at least one of the three NCDs – Type 2 diabetes mellitus (T2DM), hypertension or hypercholesterolaemia (Institute for Public Health, 2015; Ministry of Health Malaysia and Harvard University TH Chan School of Public Health, 2016). This analysis, which used a ‘care cascade’ framework, revealed major gaps in awareness of risk, timely screening, definitive diagnosis, engagement and treatment for T2DM, hypertension and hypercholesterolaemia (Institute for Public Health, 2015). The shortcomings in NCD care in primary healthcare clinics are mostly due to lack of continuity and coordination of care, poor organisational management of healthcare providers, long waiting times and limited operational hours, low screening and counselling activities, limited awareness of the need for screening services and preventive care and suboptimal therapeutic prescribing for the treatment of T2DM and hypertension (Ministry of Health Malaysia and Harvard University TH Chan School of Public Health, 2016). These findings reflect the need to address the care gaps in the health system to effectively prevent and treat CVDs.

In order to improve the performance of the Malaysian health system in managing NCDs, an integrated care model was designed to enhance existing healthcare services by incorporating public health, primary healthcare and social support as part of a ‘network’ linked to appropriate secondary and tertiary hospital services. This new framework, called ‘Enhanced Primary Healthcare’ (EnPHC), uses primary healthcare as an agent of change to deliver efficient and effective service and in turn contributes to the entire care continuum. EnPHC framework includes multiple interventions: (i) establishment of a population database with population enrolment and risk profiling, (ii) community-based intervention programmes, (iii) branding and social marketing, (iv) development of integrated multidisciplinary care pathways based on international evidence with local adaptation, (v) continuous improvement of care delivery, (vi) improved organisational practices and (vii) integrated care networks (Institute for Public Health, 2019b). All interventions are necessary for the cohesive and successful implementation of EnPHC but adaptations to the intervention are allowed.

EnPHC aims to improve management of T2DM, hypertension and hypercholesterolaemia across the cascade of care by increasing early detection and management of the target NCDs, surveillance and monitoring of diagnosed patients with improved continuity and coordination and by providing enhanced person-centred quality of care. The EnPHC framework is implemented as a demonstration project to inform decisions on further expansion to the rest of the country (Institute for Public Health, 2019b). The implementation is carried out by the Family Health Development Division of Ministry of Health Malaysia, and the evaluation is a collaborative effort between Institute for Clinical Research (ICR), Institute for Health Management (IHM), Institute for Public Health (IPH), Institute for Health Systems Research (IHSR) and Institute for Health Behavioural Research (IHBR), working with researchers at Harvard University.

The conceptual framework to guide the implementation and evaluation is discussed below. An impact evaluation that spans from the community to the patients and providers of primary healthcare is carried out (Institute for Public Health, 2019a). To further strengthen the findings from the impact evaluation studies, a process evaluation study is carried out to evaluate the implementation process in terms of fidelity and quality of implementation (Institute for Health Systems Research, 2019).

To evaluate the interventions, complementary data from multiple sources are used to measure outcomes. Evaluation performed at primary healthcare clinics aims to measure health service and patient outcomes. Therefore, the primary objective is to evaluate the impact of EnPHC interventions on processes of care and intermediate clinical outcomes among T2DM and hypertension patients, and the secondary objective is to evaluate the impact of the EnPHC interventions on patients’ experience and providers’ job satisfaction. The aim of this paper is to describe the sequential steps taken to evaluate the EnPHC interventions at primary healthcare clinics (EnPHC-EVA: Facility) and the methods used.

### EnPHC interventions

EnPHC interventions started from July 2017 and took three months for all clinics to fully implement. The EnPHC interventions represent activities in the community, facilities and networks targeting the three NCDs and risk factors (Institute for Public Health, 2019b). The EnPHC intervention is aimed at two levels which are the community and the facility level. The community level targets Malaysian adults aged 18 and above, who live within the operational area of the primary healthcare clinics. The facility level targets Malaysian adults aged 30 and above, utilising the primary healthcare clinics. The seven components of the new EnPHC framework (the intervention) are listed in the introduction and the comparison of the current public sector primary healthcare model in Malaysia, with the EnPHC framework shown in Table 1 (Institute for Public Health, 2019b).

**Table 1. tbl1:** Components of the EnPHC intervention and comparison of the current public sector primary healthcare model in Malaysia with EnPHC model

Component	Definition	Current model	EnPHC model
**(i) Population health database with population enrolment and risk profiling**			
Population catchment areas	Establishment of population catchment areas for primary healthcare clinics.	Limited availability	Available
Population health database	Development of a national population health database by data linkage from the National Registration Department and Ministry of Health. Data on screening will be entered using the MySihat Online Evaluation System (MOVeS) and fed into the database.	Limited availability	Available
Risk profiling with targeted messaging using Malaysian Non-communicable disease (NCD) risk calculator and NCD risk assessment	Systematic process of profiling behavioural and clinical health risks. Using population data, risk profiles of population groups or individuals can be developed by applying mathematical modelling focusing on hypertension and Type 2 diabetes mellitus (T2DM) and their risks being high cholesterol, obesity, physical inactivity and smoking. These stratification will be fed back to the respective District Health Office for further intervention.	Not available	Available
**(ii) Community-based intervention programme**			
Mobile health teams and community outreach efforts	Community health coordinator (CHC) is introduced at the district level, which acts as a proactive link between the clinics and the community. CHC is a medical officer (MO), who is in charge of the NCD unit in the district health office. CHC will liase with the non-govermental organisations, Healthy Community Empowers the Nation (KOSPEN), other community organisations and mobile health teams from the clinics to coordinate the following activities: (a) Health promotion and prevention (b) Health screening (c) Enrolment outreach (d) Defaulter outreach	Not available	Available
**(iii) Branding and social marketing**			
Strategic communication on health education and services to the community	Information on health education and services will be disseminated via different modes: (a) Social media (b) Ministry of Health website (c) Printed media (d) Others (e.g. local radio and state health promotion unit)	Limited	More extensive
**(iv) Integrated multidisciplinary care**			
Integrated care pathway (ICPs)	A cardiovascular care bundle that consists of ICPs—hypertension and T2DM. Care pathways are a series of management guidelines usually developed in the form of flow charts that guide care providers on how to provide treatment for all patients with a specific condition. These guidelines are designed with patient-centric ‘workflows’ and are utilised by a multidisciplinary team with specific tasks each team member at each critical step can take across the care continuum. Each ICP consists of five process elements: (a) Screening (b) Diagnosis (c) Risk profiling (d) Risk stratification and management (e) Referral	Comprehensive but designed as guidelines	Comprehensive but more operationally feasible
Visit checklist (VC)	VC is a checklist in the form of Microsoft Excel designed help family health teams (FHTs) standardise practices, improve efficiency and optimise patients’ visits. It is able to function as a ‘to do’ list in preparation for a patient’s appointment and capture current patient information such as key vital signs, lab results and medications for each visit. This will create a database on the ongoing services provided to patients.	Not available	Available through provider apps or paper-based forms to promote standardisation of care provision
Integrated specialised services (ISS)	ISS are the allied health members who are specifically trained for detailed management of cases in their area of specialisation. This includes an occupational therapist, physiotherapist, social workers, pharmacist, NCD educator, dietician and nutritionist. This would allow the MO to refer to such services and have more time to manage moderate or poorly controlled patients.	Limited availability	Available (visiting basis in most clinics)
Cardiovascular Care Bundle Medication Therapy Adherence Clinic (CCBMTAC)	CCBMTAC will be carried out by the pharmacists to assess patient compliance, conduct medication review, direct intervetion or referral to FHT and provide recommendation for those patients who have low medication adherence. Medication adherence will be assessed via both objective (medication possession ratio) and subjective (interview) measures.	Limited Medication Therapy Adherence Clinic (MTAC) service and disease specific (diabetes)	CCBMTAC covers the care bundle with structured feedback to FHT
Improve information systems for providers	A single electronic information system that integrates existing systems, provides options for manual and digital entry and supports the health system as it moves towards its long-term Tele-Primary Care (TPC) transformation.	Paper-based clinical records, legacy TPC systems and TPC-OHCIS	Paper-based clinical records, legacy TPC, TPC-OHCIS v 1.1, mobile patient and provider apps
**(v) Continuous improvement of care delivery**			
Clinical and prescribing audits	Clinical and prescribing audits are intended as routine assessments of care. Details in the indicators are available here (46).	Annual audit (e.g. National Diabetes Registry audit)	Additional indicators are measured and monthly or quarterly performance reports are generated
Secondary triage (screening and cardiovascular risk stratification)	Enhancements such as increasing the screening coverage for all the adults ≥ 30 years old; usage of NCD screening form and cardiovascular risk stratification using Framingham risk score are performed at the secondary triage. After being risk stratified, low-risk patients will be managed by assistant medical officer (AMO)/nurse, whereas medium- and high-risk patients will be managed by MO.	Screening counter is available	Available
**(vi) Improved organisational practices**			
Primary Health Team (PHT) and FHTs	Two or more FHTs are formed within a single PHT for each clinic. Each FHT will function as a multidisciplinary unit that provides services for all patients within a zone in a catchment area. At a minimum, each FHT core team will include a family medicine specialist (FMS), a MO, an AMO/nurse and a care coordinator (CC). FMSs and CCs will work on multiple FHTs within a clinic, ensuring that care across FHTs is uniform. FHT will not just assess, diagnose and manage its patients but will be responsible for educating, coordinating referral and maintaining good record keeping of each assigned zone.	Physician-centred care with limited roll out of family doctor concept (FDC)	FHTs
Primary triage and standardising signage at clinics	A primary triage and improved standardised signages are introduced to decongest the registration counter and ensure smooth navigation for patients as they go through the check points for a visit within the clinic.	Limited availability	Available
CC	CCs are essential for creating and maintaining a strong link between patients and their FHT providers. CCs will work closely with community workers, providers at screening centres and secondary and tertiary care centres to keep FHTs informed about the status of patients and any population changes in catchment areas. They are also responsible for connecting patients with support services and managing referrals and counter-referrals. CC will need a qualification of paramedic (either AMO or nurse) who has been working with the Ministry of Health and received certified training in primary healthcare or NCD management or senior paramedics with five days training in NCD management, ICP, communication and management.	Not available	Available
NCD care form	NCD Care form is a monitoring tool that includes patient health information, treatment and referral status for a specific NCD or a group of NCDs. Clinical teams will use this tool to continually assess the needs of and care provided to patients. FHTs will routinely review the forms to identify gaps in patient care and analyse data to identify where the quality of patient care may be improved. During Clinical and Prescribing Audits, data assembled will be used to study clinic performance and provide ongoing feedback about team effectiveness. NCD Care form will be used as a standardised referral document for referral to secondary/tertiary care and also referral to ISS.	Diabetic book, NCD book (Unstandardised)	Available for multiple NCDs for FHT use
**(vii) Continuity of care across healthcare facilities and communities**			
Referral and counter-referral	For advanced cases that require treatment beyond clinic capacity, patients with NCD will be referred to secondary or tertiary care. CCs will track patient referrals and counter-referrals and will continue to monitor patients along the continuum	Available but poor efficiency	Implemented by CCs
NCD Care Form	NCD Care Form will be used as the standard referral document to ensure all necessary information is conveyed during the referral process.	Referral form available but insufficient information captured	NCD Care Form with patient history and management plan

EnPHC, enhanced primary healthcare.

Note: Adapted from the Malaysia Health Systems Research Study: Implementation Plan 2016 and Enhanced Primary Healthcare Lab 2017.

### Conceptual framework

We used a health systems approach when conceptualising multiple interventions along the care cascade – as improvements in outcomes will require addressing every step in the care cascade. Care cascades have been used to examine the effectiveness and efficiency of management of infectious diseases in health systems, for example, for human immunodeficiency virus (HIV) (Gardner *et al*., 2011), Hepatitis C (Yehia *et al*., 2014), tuberculosis (Kim *et al*., 2019), as well as for NCDs such as diabetes (Prenissl *et al*., 2019a) and hypertension (Prenissl *et al*., 2019b) and examine health system performance using these conditions as tracers (Manne-Goehler *et al*., 2016; Manne-Goehler *et al*., 2019). In essence, the Malaysian care cascades for T2DM and hypertension refer to four main steps, which include proportions of patients who are (i) screened, (ii) aware of their disease, (iii) treated or advised and (iv) have their disease under control (Prenissl *et al*., 2019a; 2019b). Figure 1 shows the Malaysian T2DM care cascade which revealed that there is under-detection and under-treatment (Atun *et al*., 2016).

**Figure 1. f1:**
[figure not shown]
Care cascade for T2DM in Malaysia (Atun *et al*., 2016).

Our theory of change is that improvements in every step of the care cascade are necessary if outcomes are to improve, and the use of evidence-based integrated care pathways (ICPs), supported by the use of clinical audits (Grimshaw *et al*., 2001) and ongoing learning (Ivers *et al*., 2012) that optimised efficiency and effectiveness of services provided along the care cascade, would help improve health outcomes, user experience and user satisfaction (Baxter *et al*., 2018).

## Methods

### Study design and study sites

The EnPHC-EVA: Facility study is a quasi-experimental controlled study which involves 20 intervention and 20 control clinics. We drew on a methodology developed by Imai, King and Nall (Imai *et al*., 2009). After considering regional representativeness, budget and capacity to implement EnPHC interventions, 20 matched pairs from two states (Johor and Selangor) were selected to be the study sites. The clinics were matched based on the criteria listed in Table 2 (Family Health Development Division, 2018). In addition, ArcGIS software (ESRI, 2011) was used to ensure that the matched pairs were in different districts to minimise patients’ overlap. The matched pairs were then randomly allocated to the ‘intervention’ or ‘control’ arm of the study by ‘flipping a coin’.

**Table 2. tbl2:** Clinic inclusion and matching criteria

Clinic inclusion criteria	Clinic matching criteria
Has at least two medical officers Clinics with attendances between 300 and 800 patients per day	Number of medical officers Number of Family Medicine Specialist Location: Rural/Urban Availability of Tele-Primary Care system Annual patient attendance

There are nine and 11 matched pairs, in Selangor and Johor states, respectively. Figure 2 shows the matching pairs in both Johor and Selangor states, where intervention clinics were identified with crosses.

**Figure 2. f2:**
[figure not shown]
Selected clinic pairs in Johor and Selangor.

### Study population

The criteria for selecting the sample for each questionnaire are listed in Table 3. The different questionnaires used are described under the subheading *Data Collection Tools*. We include patients of 30 years and above to match with EnPHC interventions. Pregnant women are not included as they would have different clinical management plans.

**Table 3. tbl3:** Inclusion and exclusion criteria for retrospective chart review, patient exit survey and provider survey

	Inclusion Criteria	Exclusion Criteria
Retrospective chart review (RCR)	Malaysian Aged 30 years and above Had documented diagnosis of Type 2 diabetes mellitus (T2DM) or hypertension	Pregnant
Patient exit survey	Malaysian Aged 30 years and above Had documented diagnosis of T2DM and/or hypertension Had clinic visit for T2DM and/or hypertension on the day of survey	Pregnant
Provider survey	All permanent and visiting providers on duty in the clinic during the data collection period	Providers who served less than a month in that clinic

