### Target sample size and sampling

#### Retrospective chart review

Data analysis for RCR will use two methods – DiD analysis and interrupted time series (ITS) analysis. For DiD analysis, the sample size was calculated using *clustersampsi* in STATA version 14.2 (StataCorp, 2015).

First for T2DM, 1800 patient visits (900 in each arm) were needed to have 80% power to detect a relative change of 28% in the proportion of the patients receiving an annual HbA1c test from the baseline proportion of 52.5% (Mastura *et al*., 2011). This sample size was calculated while taking into account the estimated cluster effect [intracluster correlation (ICC) = 0.091] (Singh *et al*., 2015; Solorio *et al*., 2015). The minimum sample size was rounded up to 2000 or a cluster size of 50 patient visits per clinic. Therefore, the final target sample size for T2DM was 84 patient visits per clinic, after adjusting for an estimated 40% untraceable records.

Second, for hypertension, 1760 patient visits (880 in each arm) were needed to have 80% power to detect a 28% relative change in the proportion of hypertension patients with at least one lipid profile from the baseline proportion of 46% (Wong *et al*., 2015). This calculation took into account the estimated clustering of this outcome at the clinic level (ICC = 0.076) (Singh *et al*., 2015). After adjusting for 40% potentially untraceable records, the sample size required for hypertension patient visits was also 84 patient visits per clinic.

For ITS analysis, a minimum of 100 patient visits per arm at each time point is needed (Wagner *et al*., 2002). A minimum of eight time points was needed for both before and after intervention. In this study, eight time points pre-intervention and nine time points post 15-month intervention were chosen to evaluate the trend and level change over time. For each clinic, the estimated sample size required is ten patient visits for each disease. The final sample size after accounting for 40% untraceable records was 17 patient visits per clinic for each disease.

Systematic random sampling is used to sample the medical records by creating a sampling frame from the patients’ register either in a paper or in an electronic format. In facilities where neither of these is available, the lists are created from patient appointment books.

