#### Difference-in-differences

DiD analysis will be used to analyse all outcome measures. DiD analysis measures the average effect of the interventions, taking into account two differences: first is the difference between the intervention and control arm and second is the difference between pre- and post-intervention (Gertler *et al*., 2011; Dimick *et al*., 2014). As this is a large-scale field experiment, the difference at baseline is often not negligible and must be accounted for when measuring the intervention effect.

A multivariable model that controls for patient- and clinic-level covariates will be used. Details on the key covariates for each objective can be found in Appendix F. For RCR, patient visits from November 2016 to June 2017 will be grouped to estimate outcome levels in the pre-intervention phase and those from October 2018 until June 2019 will be grouped to estimate outcomes after 15 months of intervention.

Generalised estimating equations will be used to estimate the parameters for both linear and non-linear outcomes while adjusting for clustering at the clinic level. Thus, cluster robust standard errors will be reported. In addition, the key assumptions for DiD analysis which are ‘common shocks’ and ‘parallel trends’ will be checked where trend data are available.

The ‘geeglm’ function from the ‘geepack’ package in *R* will be used to perform the analysis (Yan, 2002; Yan and Fine, 2004; Højsgaard *et al*., 2005). For RCR outcome measures that will be reported as proportions, the DiD estimates will be reported as odds ratios with 95% confidence intervals. For provider survey and patient exit survey outcome measures, the DiD estimates will be reported as changes in means with 95% confidence intervals.

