## Discussion

The EnPHC intervention and evaluation studies aim to apply a set of multifaceted, person-centred interventions that are believed to be effective on the overall management and prevention of NCDs. This is the first study of its kind in the Malaysian context where a public health intervention involving a community outreach component, together with changes at the health system, facility, and patient level, is empirically evaluated in a ‘real-world’ setting. The community outreach component is evaluated by a separate study team and will not be discussed here. The EnPHC intervention was designed to provide organizational-level solutions such as integrated multidisciplinary care, continuous improvement of care delivery and improved organisational practices. It is aimed that, with all intervention components coming together, we will observe from the facility and health providers’ perspective increases in screening and detection rates for NCDs including T2DM, hypertension and hypercholesterolaemia and improvements in processes of care and adherence to T2DM, hypertension and hypercholesterolaemia practice guidelines. Also, it is known that workload in public primary healthcare clinics in Malaysia is so high that little time is left for meaningful interactions between patients and providers (Risso-Gill *et al*., 2015). Therefore, encouraging proactive involvement of other health professionals such as allied health allows more time for providers to strengthen patient–provider relationships and improve knowledge transfer to patients. With these multifaceted approaches, it is hypothesised that the EnPHC intervention will enhance adherence to clinic appointments and treatment and improve self-management practices and patient-reported experience at the patient level. This will subsequently improve disease control and can be measured through intermediate clinical outcomes such as HbA1c, blood pressure and lipid levels.

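### Chart-review eligibility depends on a diagnosis the package is designed to produce, so changed case mix could be mixed with the effect on care in the DiD and ITS

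*Protocol article*

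**What the plan says.** Table 3 (Study population) sets the chart-review criteria: Malaysian, aged 30 or over, not pregnant, and "Had documented diagnosis of Type 2 diabetes mellitus (T2DM) or hypertension". No date of diagnosis is required.

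The sample is a fresh draw of visits, with no fixed cohort described. Under Target sample size and sampling: "Systematic random sampling is used to sample the medical records by creating a sampling frame from the patients’ register either in a paper or in" electronic form, with appointment books as the fallback. Under Difference-in-differences, "patient visits from November 2016 to June 2017 will be grouped to estimate outcome levels in the pre-intervention phase", and these are compared with visits from October 2018 to June 2019. The ITS uses monthly chart-review data over the same observation period.

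The package is meant to find new patients. The Introduction says it works "by increasing early detection and management of the target NCDs". Table 1, component (v), describes "increasing the screening coverage for all the adults ≥ 30 years old", and component (ii) adds community screening and enrolment outreach. The Discussion expects "increases in screening and detection rates for NCDs including T2DM, hypertension and hypercholesterolaemia". The Abstract describes a large undiagnosed pool: "almost half of the patients not diagnosed".

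On adjustment, "A multivariable model that controls for patient- and clinic-level covariates will be used", with the covariates listed in Appendix F (not shown). Common shocks and parallel trends are to be checked where trend data exist. The limitations in the Discussion mention untraceable and incomplete records but not a change in patient mix.

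**The concern.** Membership of the analysed population is itself affected by the intervention. If intervention clinics detect more patients after July 2017 than control clinics do, the post-period samples in the two arms contain different proportions of newly diagnosed patients. Those patients may differ from established ones in disease control, treatment and test history. The DiD removes fixed differences between arms and shared changes over time. It does not remove a change in composition that occurs in one arm because of the intervention. In the ITS, gradual entry of such patients could appear as a change in trend.

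At stake is the primary objective, the effect on processes of care and intermediate clinical outcomes. A difference could be read as better (or worse) care of patients when part of it reflects who is being counted, and the project is meant to inform national expansion. The once-a-year indicators in Table 4 carry an added difficulty: someone diagnosed under 12 months before the visit has an incomplete look-back as a diagnosed patient.

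**Working it through.** **The plan's own figure, used as a yardstick.** The T2DM sample size targets a 28% relative change from 52.5%, that is 0.525 × 0.28 = 14.7 points, to 67.2%. With 20 clinics per arm, ICC 0.091, two-sided 5%, 80% power and t quantiles on 38 degrees of freedom:

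- Unclustered n per arm = 179.8.
- Visits per clinic m = n(1 − ICC)/(k − n × ICC) = 179.8 × 0.909/(20 − 179.8 × 0.091) = 44.9, rounded to 45.
- 45 × 20 = 900 per arm, as stated. Rounded up to 50 per clinic, 50/(1 − 0.40) = 83.3, giving the stated 84.

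This point disputes none of these figures.

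**Do the stated safeguards reach the problem?**

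- Allocation by coin flip within matched pairs balances clinics at the start. It does not govern which patients enter a register afterwards.
- Parallel trends and equivalence of baseline trends are judged on data before July 2017. A shift in mix that begins later cannot show there.
- Generalised estimating equations with robust standard errors deal with clustering, not with selection.
- Covariate adjustment could help if Appendix F includes time since diagnosis. That cannot be seen.

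**Size under a true effect of zero.** Let s and c be the post-period shares of newly diagnosed patients in intervention and control clinics, and d their outcome difference from established patients. Then

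spurious DiD = (s − c) × d.

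The document gives none of the three, so all are assumptions: c = 5%, s = 10% to 30%, d = −20 to +20 points, baseline 52.5%.

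| s | d = −20 points | d = +20 points |
|---|---|---|
| 10% | −1.0 points (OR 0.961) | +1.0 (OR 1.041) |
| 20% | −3.0 (OR 0.887) | +3.0 (OR 1.129) |
| 30% | −5.0 (OR 0.819) | +5.0 (OR 1.225) |

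For the last row with d = +20: intervention 0.525 + 0.30 × 0.20 = 0.585, control 0.525 + 0.05 × 0.20 = 0.535, difference 5.0 points, OR = (0.585/0.415)/(0.535/0.465) = 1.225. Five points is 5.0/14.7 = 34% of the planned effect. With s = c (for example 10% in both) the result is zero.

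**Is there room for a restricted analysis?** Reading the ITS target of 17 records per clinic and disease as monthly, the nine post-period months give 17 × 9 = 153 records, of which 153 × 0.6 = 91.8 are traceable, against 50 needed for the DiD. If 30% were newly diagnosed, 91.8 × 0.7 = about 64 remain. Equivalently, keeping 50 usable visits takes 50/0.6/(1 − share) records: 93, 105 or 120 for shares of 10%, 20% or 30%, all below 153. Every eligible pre-period visit qualifies, because that period ends in June 2017.

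**The case against.** The strongest reply concerns the estimand. The objective is stated for T2DM and hypertension patients, not for patients already known in 2017, and the theory of change covers every step of the cascade, screening included. For the effect on a clinic's whole diagnosed population, a repeated cross-section under randomised clinics is a legitimate design, and earlier-found patients are part of that effect. This stands. It rules out calling the current population an error, but not the need to say what the estimate contains.

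A reader might also infer that new patients enter mainly in intervention clinics and certainly bias the DiD towards better control. The document does not support that. Table 1 gives the current model a screening counter, and the Intervention checklist section expects contamination, so only an excess in intervention clinics matters. Nothing shown establishes that newly found patients have milder disease. Assuming 30% control in established patients, 50% to 60% in new ones and an excess of 10% to 20% gives +2 to +6 points (OR 1.10 to 1.31), but every input is assumed and only one sign is allowed.

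Two further points stand. Appendix F may adjust for time since diagnosis, which would reduce the problem without surely removing it. And the look-back difficulty touches only the annual indicators: blood pressure at each visit, three- and six-month measures, counselling, drug treatment and clinical targets do not need a year of history.

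**Conclusion.** The concern holds as a risk of mixing, not as a demonstrated bias. The document itself supplies the mechanism: eligibility by documented diagnosis without a date, a sample redrawn after July 2017, and a package intended to raise detection at the same ages. Neither randomisation nor the planned pre-period checks can detect or remove it.

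The direction is unknown. The illustrative range of −5 to +5 points, up to about a third of the planned 14.7-point T2DM effect, rests wholly on the assumed shares and outcome differences, and includes zero when the shares match. A reader might conclude that the main population must be replaced by previously diagnosed patients. The stated objective does not require that, since an effect on all diagnosed patients is a valid target if it is labelled as including changed case mix.

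**What to change.** - State that the all-diagnosed DiD and ITS estimate the effect of the package including any change in who is diagnosed.
- Pre-specify, as a key companion, the same DiD and ITS in both arms and both periods limited to patients whose T2DM or hypertension diagnosis is documented before July 2017.
- Report the share newly diagnosed by arm and period.
- State in advance that, if the two analyses diverge, the all-diagnosed result will not be attributed to better care of existing patients.

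Cost: some post-period visits leave the companion analysis, which the monthly sampling appears able to absorb. It needs the diagnosis date or year from each record. This is assumed available because the extraction form is not shown; with complete-case analysis, missing dates would cause further exclusions. In the post-period the restricted patients are all at least 15 months past diagnosis, so the companion result should be read against the control arm and not as a simple before-after change. The restriction also leaves untouched any shift among already diagnosed patients whom defaulter outreach brings back to intervention clinics.
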